### Participants and Recruitment

In total, 140 patients should be recruited (70 for the intervention and control group each).

Inclusion criteria: inpatients or partial inpatients (day clinic, at least 18 years old, before discharge to ambulatory care as well as outpatients, all diagnosed with MDD according to the International Classification of Diseases. All participants must have a smartphone and be generally willing to download and use a mindfulness-based app for at least 30 days.

Exclusion criteria: Acute suicidality, dementia, acute substance dependency, psychotic, schizophrenic, or schizoaffective disorders, serious health conditions like unstable cardiovascular, heart, lung, endocrine or neurological disorders, and momentary use of Headspace.

The study will be brought to the attention of potentially eligible patients of the UPK through their health care providers at UPK and through the study flyer. If they show interest in participating, the patients will receive a document with all the required information regarding the study in order to give their informed consent. After the patients sign the form of consent, it will take between 1 to 7 days until they will get scheduled for their first appointment. This will give them an adequate amount of time to consider their participation carefully. Participants will be informed about the scope and procedure of the study. Their written informed consent will be obtained.

The participants can be withdrawn from the project for any of the following reasons:

At their own request (withdrawal of consent)In case of nonadherence to the study protocol (if participants use the app on less than 25 days or if they use other courses beyond the basic course)If one or more exclusion criteria appear within the time of observation

If a participant wants to discontinue participation, this will be accepted without the need for reasons. However, the participant will be asked for potential reasons for discontinuation to document it for further analysis. The date and, if available, the reason for the withdrawal will be documented, and the participant‘s data will be destroyed.

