### Data Analysis

Basic hypothesis:

H1: Decrease (or lower increase) of the BDI-II and HDRS sum scores at T1 compared to baseline in the intervention group compared to the control group.H0: The changes in the BDI-II and HDRS sum scores between baseline and T1 do not differ between the intervention and the control group.

For the statistical analysis, we will use tools provided by the software packages IBM SPSS statistics and R (R Core Team). The changes in the symptom severity, as well as physiological parameters between baseline and T1 measurements, will be assessed. When comparing the change scores in the intervention group with those of the control group, typical hypothesis-testing, including mixed linear models, will be used, as provided by the software packages IBM SPSS statistics and R with a significance level of .05.

Sample size estimation: The estimation is based on an expected effect size of Cohen *d*=0.50, which is based on prior published studies of mindfulness-based apps. When setting the significance criterion α=.05 and β=.2 (statistical power 80%), the required sample size for a two-sample *t* test is 64 for each group. The dropout rate is expected not to exceed 10%, resulting in 140 patients overall.

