The potential immediate benefit for the participants consists of a decrease in symptom severity and prevention of depressive relapse without side effects. The long-term benefits are that patient care, especially in the outpatient setting or after discharge from inpatient treatment, will be easily augmented and improved. Moreover, the patients will be supported by an easily accessible mindfulness-based intervention. Such benefits may accommodate the issue of limited capacities in ambulatory care. With the prevention of depressive relapse, people with MDD get the chance to not only improve in symptom severity but also to live in their homes, with their families, go to school, or to work, accompanied by a tool for stress reduction.

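### Destroying the study data of participants who choose to leave, with no stated route to T1 for those who stop only the app, irreversibly removes randomised participants from the comparison

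*Protocol article*

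**What the plan says.** All the relevant wording is in the protocol article, mostly at the end of Participants and Recruitment.

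- **Grounds for withdrawal.** One ground is the participant's own wish, which the text equates with withdrawal of consent: "At their own request (withdrawal of consent". A separate ground is nonadherence: "if participants use the app on less than 25 days or if they use other courses beyond the basic course". The list says that participants can be withdrawn on these grounds, so it permits withdrawal without requiring it.
- **Voluntary discontinuation.** "If a participant wants to discontinue participation, this will be accepted without the need for reasons". Even so, "the participant will be asked for potential reasons for discontinuation to document it for further analysis".
- **What is recorded and what is erased.** "The date and, if available, the reason for the withdrawal will be documented". The same sentence ends by ordering that the participant's "data will be destroyed".
- **Analysis.** Data Analysis plans a comparison of change from baseline to T1, using methods that include mixed linear models.
- **Expected loss.** "The dropout rate is expected not to exceed 10%, resulting in 140 patients overall".

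No section says that a participant who stops using the app, but is still willing to be assessed, is invited to T1. No section says that data collected before withdrawal are kept.

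**The concern.** The destruction rule is a positive instruction, so it is not a detail left to an analysis plan, and no later analysis can restore an erased record. Its effect is that the analysed set consists of people who stayed.

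Two features make this matter here. First, the burden differs by arm. The intervention group has 30 daily sessions and weekly reminders (Intervention), the control group has only its usual care and the T1 visit (Study Design), and the trial is open-label. Leaving may therefore differ by arm in both frequency and cause. Second, the information needed to examine such a difference is what gets erased: baseline BDI-II and HDRS, setting, history and medication. Reasons are gathered for analysis, but the data that would let them be interpreted are not kept.

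**Working it through.** **1. The plan's own figures.** Inputs from Data Analysis: d=0.50, α=.05, power 80%, two-sample t test, at most 10% dropout. Taken as two-sided, the exact t test needs 63.77, so 64 per arm, as stated. Inflating for dropout, 128/(1−0.10) = 142.2, so 143. Using 63 per arm from the normal approximation, 63/0.90 = 70 per arm, or 140. The planned 140 is reproduced within rounding choices.

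**2. Loss at the plan's ceiling.** 0.10 × 140 = 14 participants, leaving 126, or 63 per arm if the loss is even. Power at d=0.50 is then 79.5%. If all 14 leave the intervention arm (56 versus 70), it is 79.0%. Power is therefore not the issue. The 14 is an upper figure for voluntary leavers, because the plan does not split its 10% by cause.

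**3. What each analysis can use.**

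| Analysis | Baseline kept, T1 missing | Baseline destroyed |
|---|---|---|
| Simple comparison of change scores | Not usable | Not usable |
| Mixed model with both visits as responses | Usable, through the baseline–T1 correlation | Not usable |
| Modelling missing T1 from baseline | Possible | Not possible |
| Leavers versus stayers at baseline, by arm | Possible | Not possible |
| Reasons by severity or setting | Possible | Not possible |
| Counts of reasons | Possible | Possible if date and reason survive; by arm if allocation is also kept |
| Tipping-point analysis | Possible | Possible if numbers missing by arm are kept |

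**4. Illustrative bias.** Let p be the share of an arm that leaves and δ how much worse leavers would score at T1 than stayers, in SD units.

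- Full-arm mean = (1−p) × stayers' mean + p × leavers' mean, so the stayers' mean is too favourable by p × δ.
- Net bias in the arm difference = (p_app − p_control) × δ, with the same δ in both arms.
- Assumed: p_app = 0.15 and p_control = 0.05, which is 10% overall, so net bias = 0.10 × δ.
- δ = 0.5 gives 0.05 SD, and 0.05/0.50 = 10% of the planned effect.
- δ = 1.0 gives 0.10 SD, and 0.10/0.50 = 20%.
- If the shares are equal, the net bias is 0. If they are reversed, it is −0.05 to −0.10 SD, against the app.

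A wider range, also assumed, has 10% to 30% leaving the intervention arm only and δ of 0.25 to 1.0. This gives 0.10 × 0.25 = 0.025 SD up to 0.30 × 1.0 = 0.30 SD, or 5% to 60% of d=0.50. The top of that range means 21 of 140 lost (15%), which exceeds the plan's ceiling.

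**5. Where the bias comes from.** It comes mainly from the missing T1 score. Obtaining T1 from people who stop the app addresses it directly. Keeping baseline data helps less: it allows leavers to be described and missing T1 scores to be modelled.

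**The case against.** The case on the other side is substantial, and several parts of it stand.

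- **A reader might infer that analysing the reasons becomes impossible.** The text does not support that. The sentence ordering destruction also says that the date and any reason are documented, and the natural reading is that these survive. Reasons can then be counted. What is lost is their link to severity, setting or course. Whether the recorded reason is itself among the destroyed data is not stated, so the two clauses need reconciling.
- **A reader might infer that everyone who stops the app is erased.** The text does not say so. Own-request withdrawal is glossed as withdrawal of consent, and low app use falls under a separate, permissive ground. What stands is that no route to T1 is described for someone who stops the app but has not withdrawn consent, and the nonadherence ground could remove that person.
- **A reader might infer that the bias could never be bounded.** A tipping-point analysis needs only the numbers missing by arm. What is lost is any analysis based on the leavers' baseline.
- **The illustration rests on assumptions.** The documents give neither the split by arm nor the gap between leavers and stayers. The 0.05 to 0.10 SD is smaller than the standard error of the comparison, √(2/63) ≈ 0.18 SD. Waitlisted controls agreed to use an app and may leave in disappointment, so the direction is open.
- **A reader might tie this to the Discussion's remark:** "The potential immediate benefit for the participants consists of a decrease in symptom severity and prevention of depressive relapse without side effects". That remark describes a potential benefit and is not an endpoint. A documented reason could also record that someone left feeling worse.
- **Destruction may be a privacy provision.** Ethics Considerations and Approval reports ethics approval and adherence to Swiss data-protection law. The consent form is not shown, so how far data may be kept cannot be judged here. Any remedy has to be conditional on that.

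None of this removes the core point: the rule is stated, it is irreversible, and it takes randomised participants out of the analysis.

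**Conclusion.** The point holds in a limited form. As written, the plan destroys the study data of participants who choose to discontinue, keeping at most date and reason, and gives no route to T1 for someone who stops only the app. Up to 14 of 140 randomised participants could be affected at the plan's own dropout ceiling, if all dropout were voluntary. Power is nearly unchanged. The cost is possible selection bias, together with the loss of every baseline-based means of examining it.

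The illustrative bias of 0.05 to 0.10 SD (10% to 20% of d=0.50) depends on an assumed 15% versus 5% split and an assumed gap of 0.5 to 1.0 SD. It shows scale and is not an estimate, its direction is not established, and destruction of baseline data is not its main source. The rule should still be changed, because erased records cannot be recovered. Recruitment was at 30 of 140 in December 2021 (Results), so 140 − 30 = 110 participants were still to be enrolled at that date.

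**What to change.** Amend Participants and Recruitment, and the consent information to match, so that two situations are separated.

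1. **Stopping the app without withdrawing consent.** The participant remains in the study, is invited to the existing T1 visit and is analysed as randomised. The nonadherence ground for withdrawal must be reconciled with this, since it currently allows the same person to be removed.
2. **Withdrawing consent.** Nothing further is collected. Data already collected are kept in coded or anonymised form, with arm, date and reason, as far as consent and data-protection rules allow. Data are destroyed only when the participant explicitly asks, and the number of such requests is reported by arm.

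State also that the documented date and reason are not among the data destroyed.

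The cost is an amendment through the ethics committee and possible re-consent of those already enrolled. No visit is added to the schedule. Some participants may still ask for erasure, and those who withdraw consent will still lack a T1 score, so the change reduces the problem without removing it.

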### Intervention

The intervention will consist of the download and the daily use of the mobile application Headspace in addition to the TAU. The participants will use the course basics of the application, which offers 10 guided meditation sessions. The duration of each session can be done in 3, 5, or 10 minutes. The study foresees that the course will be conducted in three series. The participants will make the first cycle of the course with 3 minutes per session, the second with 5 minutes, and the last one with 10 minutes per session. The participants will do one session a day, which adds up to 30 days of using the mobile application. The patients need no previous knowledge of mindfulness exercises or meditation. The course introduces and guides the patients in and through different meditation techniques. After 30 days of using the application, the patients will be examined at T1. In addition, at T1, all participants of the intervention group will be asked for short feedback about the intervention (“comment/feedback to the app use”).

To monitor the adherence to the protocol and keep participants engaged in using the app daily, participants of the intervention group will be contacted weekly via email or phone (as they prefer) and reminded of the daily use of the app.

### Secondary Outcomes

Stress levels will be examined by autonomous nervous system parameters: resting heart rate, blood pressure as well as respiratory rate. The resting heart rate, as well as the blood pressure, will be measured by using a blood pressure monitor provided by the clinic. The respiratory rate will be assessed by counting the breaths taken per minute.

The same procedures will be used for all study participants to ensure that the data from all individuals will be comparable. All measurements will be taken in awake subjects in a sitting (slightly inclined) position and in the same room. All subjects will be asked to breathe normally and not move for five minutes to reduce the impact of pretest movements.

Furthermore, all current medications (inclusive anxiolytics and sedatives), general and momentary consumption of alcohol, as well as the consumption of nicotine, in particular pack-year and amount of daily smoked cigarettes, will be assessed.

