## Methods

### Aims

The aim of this study is to assess the efficacy of a mindfulness-based mobile application (Headspace) on the symptom severity and the stress level measured by physiological parameters in patients with MDD when compared to a control group. We assume a decrease of the symptom severity, measured by the Beck Depression Inventory II (BDI-II) and Hamilton Depression Rating Scales (HDRS), in the intervention group compared to the waitlist control group. Furthermore, we hypothesize that the stress level assessed by heart and respiratory rate as well as the blood pressure will be lower in the intervention group compared to the control group.

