### Study Design

This study will be a single-center, open-label and randomized wait-list-controlled trial, which will take place at the University Psychiatric Clinics (UPK) Basel (Switzerland).

Participants will be randomly allocated to two conditions: (1) MBI mobile application Headspace+ TAU (intervention group) and (2) waitlist + TAU (control group). They will be assessed at baseline and 30 days after baseline (study end). The study flowchart is presented in Figure 1 The study started in May 2021.

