**Table 2 table2:** Study timeline.

	Time points (days)		
		Baseline (T0)	T1
	–7 to 0	0	+30
Discharge (if inpatients)	√		
Inclusion/ exclusion criteria checked	√		
Signed written informed consent	√		
Medical history, medication	√		
Participant characteristics	√		
Randomization	√		
Visit T0 (baseline)		√	
Visit T1 (study end)			√

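### The 30-session app course ends on or the day before T1, and the measurement procedure does not keep a same-day session away from the T1 vital signs

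*Protocol article*

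**What the plan says.** The Intervention section prescribes three passes through a ten-session course: "The participants will do one session a day, which adds up to 30 days of using the mobile application". Session length rises with each pass, ending with "the last one with 10 minutes per session". The follow-up visit comes straight after: "After 30 days of using the application, the patients will be examined at T1". Study Design and Table 2 both place T1 at day +30.

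Under Study Design, app-arm participants are introduced to Headspace at the baseline visit, after the baseline measurements. Controls are held on a waitlist and learn the app's name only after their T1 visit. Both arms repeat the baseline procedures at T1.

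Secondary Outcomes describes how the vital signs are taken. Everyone is awake, seated slightly inclined and in the same room, and "All subjects will be asked to breathe normally and not move for five minutes to reduce the impact of pretest movements". The section gives comparability between individuals as the reason. It does not mention whether an app session may precede the reading on the visit day, or how long before the reading the last session should have been.

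The Aims section states what these measurements are for: "we hypothesize that the stress level assessed by heart and respiratory rate as well as the blood pressure will be lower in the intervention group". Data Analysis compares the change from baseline to T1 between the arms.

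**The concern.** A guided meditation session may lower heart rate, blood pressure or breathing rate for a short time afterwards. If some app-arm participants have a session shortly before the T1 reading, the arm difference mixes two things: a change in resting stress level after a 30-day course, and the immediate after-effect of the latest session. The procedure controls one short-term influence before the test, movement. It does not control the short-term influence that differs by arm.

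What is at stake is the reading of the second hypothesis. A lower T1 value in the app arm would naturally be taken as the result of the course, and the data as collected could not tell that apart from having recently meditated.

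**Working it through.** **1. Course length, from the Intervention section.** 3 cycles × 10 sessions × 1 session per day = 30 days. This reproduces the article's own figure.

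**2. Day of the last session against T1 (day 30).** With session 1 on day s, session k falls on day s + k − 1.

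| Pattern of use | Last session | Gap to T1 |
|---|---|---|
| Start day 0, no missed day | 0 + 29 = day 29 | 1 day |
| Start day 1, no missed day | 1 + 29 = day 30 | 0 days |
| Start day 0, stops after 25 consecutive days | 0 + 24 = day 24 | 6 days |
| Start day 1, stops after 25 consecutive days | 1 + 24 = day 25 | 5 days |

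The last two rows are possible because Participants and Recruitment counts as nonadherent only those below a threshold ("if participants use the app on less than 25 days"). The interval is therefore usually short, sometimes zero, and varies between participants. A participant who starts on day 0 and makes up a missed day can also have a session on day 30.

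**3. Whether baseline subtraction or randomisation removes it.** Let L be the lasting effect of the course, p the share of the app arm with a session recent enough to matter at T1, and a the mean short-lived effect in those participants.

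- App arm, expected change = common change + L + p × a
- Control arm, expected change = common change
- Difference = L + p × a

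Baseline precedes all study use of the app, so the term p × a is zero at T0 in both arms and the subtraction leaves it in place at T1. Randomisation cannot balance it, because it is a consequence of allocation. If a session lowers the vital signs, the term has the same sign as the hypothesis.

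**4. Illustration of size. The effect sizes are assumed; the documents give none.** The number per arm is the planned 70 less the 10% dropout in Data Analysis: 70 × 0.9 = 63. As a check on the method, the two-sided two-sample t test with d = 0.50, α = 0.05 and 80% power needs 63.77 per arm, which rounds up to the article's 64. With L = 0 and a purely acute arm difference, the probability that one vital-sign test at two-sided 0.05 rejects is:

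| Assumed acute d | 63 per arm | 70 per arm |
|---|---|---|
| 0.1 | 0.09 | 0.09 |
| 0.2 | 0.20 | 0.22 |
| 0.3 | 0.39 | 0.42 |

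The nominal level is 0.05. The table shows only what follows if such an effect exists.

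**The case against.** **A visit-day rule may sit in the full protocol.** This is a fair caution, and the article is not at fault for being short. But it does set out the measurement conditions in some detail and gives comparability as their purpose. App use on the visit day belongs in that list and is absent from it.

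**The timing is looser than it sounds.** A participant who starts on day 0 and misses nothing finishes on day 29, and a session the day before is not obviously an acute exposure. Adherent participants may have gaps of 5 to 6 days. This stands, and it limits how many participants can be affected. It does not exclude same-day sessions for those who start on day 1 or make up a missed day.

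**The hypothesis does not promise a sustained effect.** This is also true. Aims says only that stress will be lower, and the Discussion disclaims middle- and long-term effects. An acute effect is not outside the wording, but the report would then have to say that this is what may have been measured.

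**The five-minute rest.** A reader might infer that sitting still with an instruction about breathing invites trained participants to meditate, so that the measurement itself creates the bias. The text does not support this. The instruction is to breathe normally, its stated purpose is to reduce the effect of earlier movement, it applies to all subjects, and the T1 procedures repeat those at baseline. Nor does the section say that the readings are taken during those five minutes. It is an ordinary settling period.

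**Conclusion.** The point holds in a limited form. The course ends on or the day before T1 for anyone who follows the full schedule. The described procedure does not separate a same-day session from the vital-sign readings. Any short-lived effect would fall by design on the app arm alone and would survive the change-score comparison.

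The size is unknown. A reader might infer that the bias could rival the d = 0.50 used for the sample size. For example, half the arm affected, a fall of 2 to 4 breaths/min and an SD of 3 would give 0.5 × 2 / 3 = 0.33 to 0.5 × 4 / 3 = 0.67. None of those three inputs is in the documents, and the trial was sized on depression scores, so the comparison shows nothing about this trial.

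Only the secondary vital-sign outcomes are affected. This point does not touch the BDI-II and HDRS comparisons or the sample size. The conclusion assumes that no visit-day rule exists elsewhere and that a session has some brief effect on these measures. It is a modest point, worth acting on because the remedy costs very little.

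**What to change.** - In the Intervention and Secondary Outcomes sections, ask app-arm participants to do no session on the T1 day until their vital signs have been taken.
- Record at T1 the time since the last session. This also covers sessions late on the day before and the longer gaps of participants who missed days.
- Leave the rest instruction and the order of procedures identical at T0 and T1. Rewording the breathing instruction, counting breaths unannounced or moving the vital signs to the start of T1 only would break the match between the two visits that the change score relies on.
- If the rule is not adopted, state that the vital-sign result may include an acute effect of a recent session.

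The cost is one visit instruction and one extra field at a visit that already takes place. Participants measured at T1 before the rule applies should be flagged in the data. With 30 of 140 enrolled by December 2021, 140 − 30 = 110 were still to come at that date, so most of the sample could be measured under the rule if it were introduced then.
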